#### **c. Usual care**

Participants in G3 will receive standard care. This will include being provided with standard oral care recommendations. Participants in all groups will receive the same recommendations.

### **C.5 Evaluation**

All questionnaires will be administered at the patient's clinic visits. If, however, there are time constraints, patients will be given a self-addressed stamped envelope in which to return the questionnaires. Baseline assessments will be completed within 7 days prior to starting radiotherapy, and patients will then complete the same assessments again at middle and end of radiotherapy and 2-4, 5-9, and 10-15 months after the end of radiotherapy. At middle and end of radiotherapy, data will be collected before acupuncture treatment. For patients at

Fudan Cancer Hospital, the questionnaires were forward and backward translated into Mandarin Chinese (the MDASI and FACT-G were also validated in Mandarin Chinese; see Appendix H). All of the questionnaires and saliva collection techniques have been used successfully at both institutions.

To determine if true acupuncture is more effective than sham acupuncture or standard care for reducing the incidence of radiation-induced xerostomia we will evaluate xerostomia graded according to Common Terminology Criteria for Adverse Events (CTCAE) (78) (see Appendix I).

**a. Xerostomia and quality of life questionnaires**

i. Xerostomia Questionnaire (XQ): The XQ is an 8-item questionnaire that has been validated in several cohorts (22, 74). Subjects rate each symptom on an 11-point ordinal Likert scale from 0 to 10, with higher scores indicating greater dryness or discomfort due to dryness. The item cores are added and the sum is transformed linearly to produce a final summary score ranging between 0 and 100, with higher scores representing more xerostomia. The clinical response of the XQ has been suggested by Eisbruch (22) and Pacholke research (74) with XQ scores  $\leq 30$  regarded as mild to no symptoms of xerostomia. This measure may also be collected over the phone if the patient is unable to come to MD Anderson.

ii. The Functional Assessment of Cancer Therapy (FACT-G): Health-related quality of life will be assessed with the FACT-G (77). This instrument is able to discriminate between individuals with metastatic and non-metastatic disease, as well as between patients at different stages of illness. The scale has been found to have good concurrent validity, high internal consistency (0.89), and good test-re-test reliability (0.82 to 0.88).

iii. M. D. Anderson Symptom Inventory for Head and Neck Cancer (MDASI-HN): Cancer-related symptoms will be assessed using the validated MDASI-HN (75, 76). The MDASI measures, on a numeric rating scale of 0-10, both the severity of symptoms and the interference symptoms cause in patients' daily activities. The 13 core MDASI symptom items are based on extensive evaluation of symptoms common to cancer and cancer treatment. The MDASI-HN includes 9 head and neck-specific items. The instrument was validated in a cohort of more than 200 patients and found to be highly reliable (76).

iv. Fatigue will be assessed using the Brief Fatigue Inventory (BFI) [95]. The BFI is a 9-item questionnaire designed to be used in the clinical setting to rapidly assess fatigue severity. The items are ranked from 0 to 10, and patients rate their fatigue at its "worst" and "usual" and as it is "now," with 0 = "no fatigue" and 10 = "fatigue as bad as you can imagine." Patients also rate how much their fatigue has interfered with their life. This single-dimension instrument was tested in a sample of 305 patients with cancer, and provided an internally stable measure of fatigue severity (0.80-0.92) [95].

v. The Brief Pain Inventory (Short Form) is a validated, widely used, self-administered questionnaire to assess severity of pain and impact of pain on daily functioning among patients (101-103). Item 1 assesses whether or not patients are currently experiencing pain other than minor headache, sprain, or toothache. Item 2 allows patients to indicate on a whole body diagram the exact location of pain. Items 3-6 measure severity of pain on a 0-10 numeric scale. Item 7 assesses current treatment and item 8 assesses relief from pain treatments or medications within the last 24 hours. Finally, item 9 includes 7 subratings

regarding the impact pain within the previous 24 hours has had on patients' QOL.

vi. Depression will be assessed using the Centers for Epidemiological Studies-Depression measures (CES-D) [98]. The CES-D is a well-validated 20-item self-report measure of depression that focuses on affective components of depression. Respondents rate the frequency of the behavior or feeling using a 4-point Likert-type scale ranging from "almost never" to "almost always." The internal consistency of the instrument is high in the general population and in patient populations. It also has demonstrated adequate convergent validity with other measures of depression [98].

vii. To thoroughly evaluate social processes, we will assess the availability of social support perceived by participants, the frequency and quality of their social interactions, and the level of expression of emotions with others. Perceived availability of social support will be measured using the Medical Outcomes Study Social Support Survey (MOS-SSS) [99], which was developed with the SF-36 quality of life index and other MOS measures in one of the largest and most comprehensive studies of health status in the chronically ill. The scale focuses on the perception of the availability of functional support. Patients rate the perceived availability of: emotional/informational support, tangible support, positive interactions, and affectional support. Internal consistency was high, ranging from 0.91 to 0.96, and test-retest reliability ranged from 0.72 to 0.76. It has good predictive validity reflecting significant relations between social support and overall health status [100]. We have also added a few questions that ask how satisfied they are with the contacts.

viii. Two items assessing behavioral and characterological self-blame for patients' cancer cause will be administered based on previous work in breast cancer patients (96). Patients will also complete two treatment regret items previously used by Hu et al. in a sample of prostate cancer patients (97). These questions will take about 1 minute to complete.

ix. Self-report measure of oral hygiene will be assessed weekly during radiotherapy, and then 2-4, 5-9, and 10-15 months after the end of radiotherapy. Patients will be asked to indicate in the past week the frequency with which they brushed their teeth, flossed their teeth, and estimate how much water they consumed on daily basis.

x. Self-report measure of other acupuncture will be assessed at the middle of radiotherapy, end of radiotherapy, and at 2-4, 5-9, and 10-15 months after the end of radiotherapy. Participants will be asked to indicate if they have received any acupuncture that is not study related as well as the frequency, indications it was received for, and any benefit experienced. If any participant has received acupuncture that is not study related, we will request contact information of the provider(s) in order to obtain the acupuncture points used in the treatment. This measure may also be collected over the phone if the patient is unable to come to MD Anderson.

#### **b. Saliva flow examination**

Unstimulated Whole Saliva (USFR): Patients are instructed to refrain from eating, drinking, and dental hygiene for a minimum of 60 minutes before saliva collection. The patient is seated upright in a quiet area where he/she will remain undisturbed and to minimize orofacial movements. The patient will relax in the designated area for 15 minutes before saliva collection. Patients are instructed not to attempt to increase or control salivation actively (such as sucking or swallowing) but to simply relax. A collection vial (including seal and cover) will be weighed on a calibrated balance with accuracy to 0.001 gm. The patient is instructed to first clear his/her mouth by swallowing. Then, with the head held slightly forward, the patient is

instructed not to talk or swallow during the 5-minute collection but to allow saliva to collect in the floor of the mouth. The 5-minute collection time is initiated on a digital timer and in view of the patient. The patient should then expectorate the accumulated saliva into the pre-weighed vial after 60 seconds. The patient should repeat this procedure 4 more times for a total collection time of 5 minutes. Patients are reminded not to swallow during the entire collection period. At the end of the 5 minutes, the collection vial is promptly sealed, weighed, placed on ice and transported to the laboratory.

Stimulated Whole Saliva (SSFR): Patients are to rest for 5 minutes prior to stimulated saliva collection. The exogenous stimulant will be a neutral chewing gum from Wrigley (unflavored gum base) used previously for SSFR. The patient will chew the gum for 3 minutes, then expectorate the gum and saliva into a disposable cup. Next, the patient should swallow to clear the mouth. The patient's saliva will then be collected in the vial for 5 minutes using a method identical to USFR collection. After a 5 minute rest period, repeat (i.e. chew gum for 3 minutes, expectorate gum and saliva into a disposable cup, swallow, then collect saliva for 5 minutes as above.)

#### **c. Saliva constituent analyses**

We will determine acupuncture's effects on saliva-based factors including pH, buffering capacity, and viscosity as well as levels of total protein, CGRP and VIP from SSFR collected at baseline, end of radiotherapy (week 7), and 2-4, 5-9, and 10-15 months later. The value of pH and buffering capacity will be measured using a portable pH meter with micro electrode. Buffering capacity will be measured using the method previously described by Siqueria et al. (79). Buffering capacity and pH will be conducted on fresh saliva. Viscosity, total protein, CGRP, and VIP will be measured at M. D. Anderson from frozen samples assayed in batch to decrease variance. Viscosity of the saliva (0.5 ml) will be determined using LVT Wells-Brookfield cone-and-plate digital viscometer (Brookfield Engineering Laboratory) (80). The total amount of protein in each saliva sample will be determined using the Bradford assay (Biorad protein assay kit). Levels of CGRP and VIP will be quantified using neuropeptide-specific RIA kits (Peninsula-Bachem) (81). The concentration of peptides will be normalized by the amount of protein in each sample. All assays will be conducted in the laboratory of [name]. Once the saliva samples have been assayed they will be destroyed.

#### **d. Expectations**

Acupuncture Expectancy Scale (AES): To determine the relationship between outcome expectancy related to acupuncture and clinical response, we will use the Acupuncture Expectancy Scale. This 4-item instrument was developed by Mao et al. and found to be reliable (Cronbach's  $\alpha$  of 0.82) and valid by positive correlation with patient self-reported efficacy and satisfaction (61). The scale was further validated among cancer patients who were mostly acupuncture naïve (57). Expectancy of a benefit from acupuncture appeared to be increased by educating patients on the scientific theory and clinical evidence of acupuncture. Higher expectancy was also found in patients who had previously participated in an acupuncture trial compared with those who had not participated in an acupuncture trial (57). The scale has been translated and validated in Mandarin in China. In the proposed study, we will evaluate expectancy as a predictor of response to acupuncture. This questionnaire will be completed at baseline by all participants. Patients in the acupuncture treatment groups will complete the form again during the middle and at the end of radiotherapy.

#### **e. Background/Exposure**

Background/Exposure Questionnaire variables: The purpose of this questionnaire is to collect information on environmental and occupational exposures, phenotypic characteristics, health history, family history of cancer, and behavior patterns that could be associated with cancer of the head and neck. The data collection instrument will be comprised of the interview-based questionnaires that are currently used at MDACC. The questionnaire includes questions on the following items:

- Demographic data, including name, address, date and place of birth, marital status, ethnicity, total years of education, and income.
- Tobacco and alcohol exposure, including past and present smoking and drinking status, number of years smoked/drank, and number of cigarettes smoked or drinks consumed per day.
- Behavior patterns that could affect an individual's exposure.
- Medical history information on previous health such as history of cancer, immune conditions, and hormone and x-ray treatment.

## **C.6 Statistical Considerations**

As our first step, before analyses, we will conduct extensive descriptive analyses on the data collected at baseline and at each follow-up. Descriptive statistics (i.e., frequencies, ranges, means, proportions, standard deviations, measures of skewness and kurtosis), including 95% confidence intervals (CIs), will be computed for the measures. We will closely examine distribution characteristics of the variables using box plots, histograms, scatter plots, and the Kolmogorov-Smirnov test of normality where appropriate. Distribution assumptions will be evaluated, and if indicated, normalizing transformations or robust procedures will be used. We will evaluate bivariate associations between the outcome measures and selected demographic and disease-related variables, including age, ethnicity, time since diagnosis, and disease stage, using Pearson product-moment correlation coefficients, chi-square, or eta-squared estimates from analyses of variance where appropriate.

### **a. Data analysis**

Our primary objective is to determine if true acupuncture is more effective than sham acupuncture or standard care for preventing radiation-induced xerostomia among cancer patients at M. D. Anderson and Fudan Cancer Hospital. The primary outcome will be self-reported xerostomia symptoms using the Xerostomia Questionnaire (XQ). We will have information available at baseline and at 5 additional points in time (middle of radiotherapy, end of radiotherapy, and 2-4, 5-9, and 10-15 months after the end of radiotherapy).

Our initial analysis will be a repeated-measures analysis of XQ scores over time by acupuncture group, testing for group effects, time effects, and group by time interaction. This will be done using generalized linear mixed model regression (GLMM) (see below for further details). The primary significance level which will be used is

0.05. For sample size justifications, our primary time endpoint is the end of radiotherapy, or 7 weeks. All three arms will be compared at this time point using an analysis of variance, and if the test is significant ( $p < 0.05$ ), we will use a Duncan's Multiple Range Test which controls the type I comparison-wise error rate to determine which groups are different from each other.

At each point in time, we will also be able to determine if xerostomia has occurred (grade 1 or higher on the v3.0 CTCAE) and will classify each patient as either experiencing xerostomia (one or more episodes of xerostomia) or not. A secondary goal is to determine if the proportion of persons who experience xerostomia in the true acupuncture group is less than that in the sham acupuncture group or the standard care group. We will use the

binomial test to test for these differences at each follow-up. We will also use the clinical response criteria of determining whether or not xerostomia has occurred or not as used by Eisbruch (22) and Pacholke (74). A significant response will be indicated if the summation XQ score  $\leq$  is 30. Eisbruch and colleagues revealed with bilateral radiation therapy treatment, the peak effect of XQ xerostomia scoring at 3 months post treatment is 45 +/- 10 (22). Using the criteria of  $\leq$  30 on the XQ score, we will use the binomial test to test for these differing proportions between groups at each follow-up. However, if 15 tests are made, in order for the results to be considered as significance as those with a 0.05 significance level, the significance level would need to be 0.003 or less (0.05/15) using a conservative Bonferroni method. We will also include a GLMM analysis to evaluate treatment and time effects upon incidence (general patterns in incidence). This analysis will test the overall treatment effect, the overall time effect and a treatment by time effect.

Other outcomes include the MDASI-HN, FACT-G, USFR, SSFR, and saliva constituents including pH, buffering capacity, and viscosity as well as levels of total protein, CGRP, and VIP. These variables are repeated measurements on multiple outcomes, possibly including hierarchical structure over subscales and related outcome measures. Desired inference includes hypotheses about treatment effects at different times and on different outcomes. Also, inference about treatment effects has to appropriately adjust for recorded baseline characteristics of the enrolled patients. With these considerations in mind, we propose the following strategy for the data analysis of these variables. As we expect scores on the criterion measures to be correlated within individuals over time, we will use GLMM. Separate sets of analyses will be conducted for each criterion variable (e.g., primary outcome: severity of self-reported xerostomia symptoms (XQ); secondary outcomes: MDASI-HN, FACT-G, saliva flow rates, and saliva constituents). For each criterion variable, we will use data across the set of post-intervention assessment points. In modeling these data, intervention condition is a between-subjects factor, time is a within-subjects factor, and baseline measures will be included as covariates.

GLMM is a flexible analytic approach with wide use in the health sciences (82). Mixed model regression allows for repeated measures across individuals by modeling the correlation among the repeated measures. GLMM can accommodate a range of correlation structures among the measures, as well as continuous and discrete outcome distributions, unbalanced designs, different link and variance functions, and, in the case of the analysis of independent data, is equivalent to logistic, ordinary least squares regression, or analysis of covariance modeling.

For the GLMM, first we will assess the covariance structure of the data so that inferences about means are valid. We cannot assume that repeated measures for an individual will be equally correlated because two measurements taken at adjacent times may be more highly correlated than two measurements taken several time points apart. To select the best method for modeling the repeated measures, we will use the methods of Wolfinger (83) and statistics such as Akaike's and Schwarz's information criteria.

After determining the appropriate covariance structure, we will develop longitudinal models of the effect of intervention condition on post-intervention (follow-up) criterion measures that take into consideration the baseline values for the corresponding criterion measure as well as important covariates. Mixed model parameter estimates and tests will allow us to compare intervention effects and to examine intervention effects over the course of follow-up time

points. Post-intervention follow-up criterion measures will be regressed onto study intervention condition, time of assessment, a polynomial function of time (for example, quadratic) if appropriate, and the measure of the criterion at baseline. In addition, we will add important covariates, including adaptive randomization variables and selected demographic variables, such as ethnicity and education, as well as suitable baseline health-related variables and medical characteristics. Tests of the interaction of intervention condition with time of measurement will be evaluated to determine whether the effect of intervention condition varied as a function of time. In the case of statistically significant interactions of intervention condition with time, tests of the effect of intervention condition will be conducted at each individual time point. We will use Bonferroni corrections for each set of multiple comparisons where appropriate. Standard methods of model diagnostics will be used to identify influential observations and to determine suitable transformations where necessary.

We will compare compliance with acupuncture between patients randomized to the acupuncture and sham acupuncture groups. Compliance will be measured as the number of times the participants received their scheduled intervention per week. At each assessment after the end of radiotherapy, we will determine if patients in the two groups differ in the number of times they received their scheduled intervention (since the last analysis) using a Wilcoxon rank-sum test. We expect that these frequencies will not be normally distributed so we plan to use a nonparametric test. If there is a statistically significant difference or trend for significance in compliance between any two groups ( $p < 0.10$ ), we will also determine if there is a difference between other outcomes. We will use either t-tests or nonparametric tests such as the Wilcoxon rank-sum test to determine the significance of these differences.

We will also explore the association between expectancy and outcomes using information from the Acupuncture Expectancy Scale (AES). Expectancy will be assessed using the AES at baseline in the acupuncture and sham acupuncture groups and will be correlated with severity of xerostomia using the XQ (and other continuous variables) during and after radiotherapy. More complex analyses will also evaluate whether expectancy moderates outcomes. Following the procedures of Baron and Kenny (84), the evaluation of moderation involves examining the interaction between intervention condition and baseline expectancy. In a series of mixed model analyses, tests of the interaction of intervention condition with expectancy will be evaluated to determine whether baseline expectancy changes the impact of acupuncture condition on the outcome measures [i.e., determine whether acupuncture (active or inactive) is more effective based on baseline expectancy]. Changes in USFR, SSFR, and saliva constituents will also be examined as possible mediators of the effects of acupuncture on xerostomia symptoms following the procedures of Baron and Kenny (84) using generalized linear mixed model regression. The mediation effect estimate will be computed according to MacKinnon (85), who describes mediation as the difference of the intervention effect on outcome with and without the presence of the mediators, or alternatively, the product of the effect of the intervention on the mediators and the effect of the mediators on the outcome controlling for the intervention condition.

We will evaluate the data on a yearly basis by performing a yearly interim analysis. Our primary outcome is self-reported xerostomia symptoms using the Xerostomia Questionnaire (XQ). At each interim analysis, we will examine the difference in change scores (between baseline and the end of radiotherapy or 7 weeks) of the XQ between arms. If the true acupuncture arm is less effective than other arms and this comparison is statistically significant at  $< 0.001$ , we will terminate the study early (Peto method). These interim analyses will not affect the significance level of the final analysis. In order to address safety concerns, at each interim analysis we will also evaluate the incidence of grade 3 or higher adverse events in each arm separately. If patients in any arm experience more than 20% patients

experience grade 3 or higher adverse events that are either definitely or probably related to acupuncture treatment, we will terminate that arm early.

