#### PRIMARY AIM

1. Determine if true acupuncture is more effective than sham acupuncture or standard care for preventing radiation-induced xerostomia among cancer patients at M. D. Anderson and Fudan Cancer Hospital. The primary outcome will be self-reported xerostomia symptoms using the Xerostomia Questionnaire (XQ).

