#### **c. Sample size calculations**

These precision and power estimates are based on a final post-intervention sample size of 300 study participants, 100 in each of the three intervention groups. To achieve this post-intervention sample size, we will oversample by 31% (i.e., 435 participants) to account for attrition. That is, we will allow for up to a 31% drop- out rate.

Our primary analysis is a mixed model regression analysis with repeated measures to evaluate the between group differences across the post-intervention time points with adjustment for covariates. Assuming a two- sided significance level of 0.05, we will have at least 80% power to detect differences between any pair of group means of 0.4 standard deviation units (SD – Effect Size Index) across the three post-intervention time points. In addition, the detectable mean difference between groups is 0.49 SD units with a two-sided significance level of 0.01. In our previous study, we found differences on post-intervention XQ means ranging from 0.80 SDs at the end of radiotherapy to 0.68 SDs at 1 month when comparing the acupuncture group with the standard care group. The associated XQ average values for the two groups at 1 month post radiotherapy were: 32.2 (SD=10.6) for acupuncture group and 41.5 (SD=9.6) for control group. As we do not know the exact differences that will occur between the sham acupuncture group and the other two groups, and given the definition of clinically significant effects (i.e., effect sizes of approximately 0.5 SDs being argued to be clinically meaningful) (25, 86, 87) the current study is still well-positioned to detect clinically significant effects between groups that may be present. We prefer to justify sample size using a paired t-test for simplicity and because it is conservative approach, although the later analyses using repeated measures will have greater power to detect differences between groups.

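### The final plan does not say which XQ test, over which visits, decides the primary aim

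*Supplement*

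**What the plan says.** All references are to the Final Protocol, which holds the analysis plan in section C.6.

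- **Primary Aim.** It fixes the instrument, the self-reported XQ score, but no time point.
- **C.6 a, visits.** "We will have information available at baseline and at 5 additional points in time": mid-radiotherapy, end of radiotherapy, and 2-4, 5-9 and 10-15 months afterwards.
- **C.6 a, longitudinal model.** "Our initial analysis will be a repeated-measures analysis of XQ scores over time by acupuncture group", with tests of group, time and their interaction. "The primary significance level which will be used is" 0.05; the sentence does not attach that level to any one test.
- **C.6 a, single time point.** "For sample size justifications, our primary time endpoint is the end of radiotherapy, or 7 weeks". All three arms are then to be compared at that visit by ANOVA and, if p < 0.05, by Duncan's test.
- **C.6 c.** "Our primary analysis is a mixed model regression analysis with repeated measures to evaluate the between group differences across the post-intervention time points", adjusted for covariates. Power is stated over three such time points, which are not listed. The same section then says that the number of patients is justified by a paired t-test.
- **C.6 a, interim analysis.** "we will examine the difference in change scores (between baseline and the end of radiotherapy or 7 weeks) of the XQ between arms".

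C.6 a also promises Bonferroni corrections within sets of multiple comparisons where suitable. It does not say how the ANOVA and the longitudinal tests relate to each other.

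**The concern.** The ANOVA asks about dry mouth at the end of treatment. A model averaged over several visits asks about the course of symptoms, possibly up to 15 months later. A treatment could succeed on one and fail on the other. The plan attaches the word primary to a time point in one place and to a different analysis in another, and gives no rule for a disagreement. The choice could then be made after the data are seen, and a reader could not tell. The 5% error rate of the main claim would hold only if the choice were fixed beforehand.

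**Working it through.** **1. Which test does the stated sample size match?** Inputs from C.6 c: 100 evaluable per arm, difference 0.4 SD, two-sided 0.05, power at least 80%, dropout 31%, 435 enrolled.

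- Two-sample comparison at one visit: n per arm = 2(1.960 + 0.842)² / 0.4² = 98.1, so 99.
- Power with 100 per arm: Φ(0.4·√50 − 1.960) = Φ(0.868) = 80.7%; with the noncentral t, 80.4%.
- Second stated figure, 0.49 SD at two-sided 0.01: 81.3% (noncentral t 80.5%).
- Enrolment: 300 / (1 − 0.31) = 434.8, so 435.

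The plan's figures therefore reproduce as a comparison of two independent arms at a single visit. The alternatives do not match:

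- Mean of three visits, with equal between-visit correlation ρ: the variance is (1 + 2ρ)/3 of the single-visit variance. Power at 0.4 SD is 97.2%, 93.4% and 88.5% for ρ = 0.3, 0.5 and 0.7.
- Paired t-test with 100 pairs and 0.4 SD of the differences: 97.7%. Independent arms provide no pairs in any case.

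**2. Error rate if either test may be claimed.** If the two tests were independent, the chance of at least one false positive would be 1 − 0.95² = 9.75%. They share patients, so the true value is lower and depends on the correlation between visits. The documents give none, so it is varied here.

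Null simulation: 3 arms × 100, five visits, 6,000 runs per row. The ANOVA is at visit 2 (end of radiotherapy). The longitudinal group test is a one-way F test on each patient's mean over visits. Because C.6 c does not define its three visits, two visit sets were tried: all five, and the last three.

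| Correlation (assumed) | ANOVA alone | 5-visit mean alone | ANOVA or 5-visit mean | ANOVA or mean of last 3 |
|---|---|---|---|---|
| Equal, 0.3 | 4.9% | 4.9% | 8.5% | 9.2% |
| Equal, 0.5 | 5.0% | 5.1% | 8.1% | 8.7% |
| Equal, 0.7 | 4.9% | 5.1% | 7.6% | 8.0% |
| AR(1), 0.5 | 4.9% | 5.0% | 8.4% | 9.3% |
| AR(1), 0.7 | 5.2% | 4.9% | 7.8% | 9.0% |

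The Monte Carlo standard error of the union columns is about √(0.08 × 0.92 / 6000) = 0.35 percentage points. Further runs of 20,000 per scenario gave 7.2 to 9.2%. Each test alone holds 5%; the excess comes only from leaving the choice open.

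**3. Is the Duncan step the source?** No. With the F test as a gate and 100 per arm, the chance of any false pairwise claim was 5.0% when all arms are equal. It was 4.7 to 5.1% for the remaining null pair when one arm differs by 0.3 to 0.8 SD.

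**The case against.** The best defence is that the plan has one primary analysis. Only the mixed model in C.6 c is literally called that. The repeated-measures model in C.6 a can be read as the same model, and the end-of-radiotherapy endpoint is introduced as serving the sample size. On that reading week 7 is a planning device. A reader who infers two or three declared primary analyses, each with its own 0.05, goes further than the text: there is one stated primary significance level, an ANOVA threshold, and a 0.05 used as a power assumption. That much of the defence stands.

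It does not settle the matter. C.6 a still prescribes the week-7 ANOVA and Duncan's test on the trial data. The sample size section, which week 7 is said to serve, states power over three visits instead. The mixed model itself has no defined visit set: C.6 a lists five post-baseline visits, its modelling paragraphs speak of post-intervention assessments in general, and C.6 c counts three.

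Three stronger readings are tempting and not supported:

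- **That end of radiotherapy is excluded from the primary model.** The three visits might be taken to be those at 2-4, 5-9 and 10-15 months. But when C.6 c reports the previous study, it counts end of radiotherapy among the post-intervention XQ results, whereas C.6 a equates post-intervention with follow-up. The set is unclear; exclusion is not shown.
- **That the error rate is 12 to 16%.** Figures of 14 to 16% arise if any unadjusted pair on the three-visit mean counts as a win, which ignores the Bonferroni wording in C.6 a. With Bonferroni pairs the figure is 7.4 to 8.8%. Figures near 12% count a significant group-by-time test as a win. In the plan that test leads to visit-specific tests; alone it does not show that true acupuncture is better.
- **That the interim rule adds another route to success.** It stops the trial only if true acupuncture is worse.

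**Conclusion.** The concern holds in this form: the final plan leaves open which XQ test, over which visits, decides the primary aim. This is a conflict between C.6 a and C.6 c, not merely missing detail. If a positive result on either the end-of-radiotherapy ANOVA or the longitudinal group test could be called primary, the type I error is about 7 to 9% instead of 5%. That size rests on 100 evaluable per arm, complete data without covariate adjustment, and assumed between-visit correlations of 0.3 to 0.7. It is conditional, because the plan neither permits nor forbids the either-or claim. The stated sample size itself is sound as a single-visit comparison.

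A reader might also infer that true acupuncture must be tested against sham first and against standard care only afterwards. The plan sets no such order. That is a design preference, not a correction the text requires.

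**What to change.** Name one primary estimand and one deciding test at two-sided 0.05, and bring C.6 a and C.6 c into line with it, including the modelling paragraphs on which visits enter the model.

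The choice best supported by the plan is the XQ contrast at end of radiotherapy, estimated from the baseline-adjusted mixed model. C.6 a names that time point, the interim rule uses it, and the stated power reproduces as a single-visit comparison (80.4%). Then:

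- list the visits that enter the model;
- label the across-time group effect, the group-by-time test, the later visits and the ANOVA with Duncan's test as secondary or supportive;
- state how error is controlled over the two comparisons with true acupuncture (versus sham and versus standard care); a fixed sequence is one option;
- replace the paired t-test wording with the two-sample comparison that gives the stated figures.

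The cost is plan wording and a short protocol amendment. The numbers stay at 300 evaluable and 435 enrolled, with no added data. The downside is that the longitudinal group effect can no longer be claimed as primary. Naming the longitudinal test instead would also restore 5%. Keeping both as alternative routes at 0.025 each would hold the error rate, but single-visit power at 0.4 SD would fall to about 71.5% with 100 per arm, and 80% would need 119 per arm.
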